### Sample size

2.5

We were unable to perform a sample size calculation owing to the absence of a prior study that compared real-BCI and sham BCI using the identical BCI system. Consequently, we have established a sample size of 20 for each arm, adhering to the minimum number suggested for pilot trials (32).

### Recruitment

2.6

People will be recruited at the National Rehabilitation Center according to the inclusion and exclusion criteria.

### Assignment of interventions: allocation and blinding

2.7

Forty patients with stroke will be enrolled in this study. The random number table, which assigned the participants to either the real-BCI group or the sham-BCI group, was generated by PASS in the order of recruitment of participants. An external researcher will create a random number table and maintain it until the end of the study. The assignment will proceed by opening an opaque envelope containing a random number table in the order of participant recruitment. All participants will be blinded without knowledge of the group they will be assigned to.

### Data collection and management

2.8

#### Plans for assessment and collection of outcomes

2.8.1

All the participants will complete a baseline assessment before commencing the intervention. Then, assessments will be performed 2 weeks after starting the intervention (after the 10th session of intervention) and after the completion of the intervention (after the 20th intervention session). A follow-up test will be performed 4 weeks later. An experienced research physical therapist will conduct all clinical assessments and EEG testing, and physiatrists will perform TMS measurements. The assessments will be conducted without the participants knowing their assigned group. All data in this study will be recorded and managed using the data management software in Microsoft Excel. All researchers will use an encrypted computer to record and save data to ensure data security, with backup data to prevent data loss.

### Plans to promote participant retention and complete follow-up

2.9

Patients at our hospital can be hospitalized for up to 3 months, providing sufficient time for follow-up evaluation (T8). Follow-up evaluation will be conducted after finishing the intervention.

### Data management

2.10

All data will be stored electronically. The approved case report form (CRF) will be saved by coding at the end of the patient evaluation. The evaluator will conduct a clinical evaluation on paper and transfer it to the CRF. In addition, in the case of evaluation using medical equipment, such as EEG and MEP, files will be created and stored for each patient ID. Monitors, inspection personnel, and the National Rehabilitation Center Clinical Trial Review Board will not directly view or submit research-related data to verify the reliability of the procedure and data of this study within the scope stipulated by the relevant regulations, without infringing on the confidentiality of the research participants. In addition, the analysis will be conducted using only the study ID and raw research data. Personal identifiable information will be securely destroyed after being stored for 3 years after completion of the study.

### Statistical methods

2.11

A repeated-measures analysis of variance at the time level (T0, T2, T4, and T8) will be applied to examine whether primary, secondary, and neurophysiology outcomes improved after the intervention. Paired t-tests will be used as post-hoc tests to examine significant changes in different combinations of time points for the scores. The normality of the data will be checked using Kolmogorov–Smirnov tests, and the results will show whether the data are normally distributed. The Bonferroni correction will be used for multiple comparisons.

The Friedman test will be performed for within-group comparisons between time points for non-normally distributed data. The Wilcoxon signed-rank test will also be used for within-group comparisons at each point in time. The resting-state EEG data (with eyes closed) will be first preprocessed to analyze the changes in functional connectivity in the motor area before and after the intervention. The raw EEG data will first be filtered using a 3rd-order Butterworth filter with 1 and 50 Hz cutoff frequencies. Subsequently, it will be divided into 1-s epochs without overlaps. Epochs showing large artifacts, detected using a signal threshold of ±120 μV, will be removed. Next, 30 artifact-free epochs will be randomly chosen for each participant. Partial directed coherence (PDC), a representative effective functional connectivity measure, will be used to evaluate changes in directed functional connectivity from the premotor area to the motor area before and after the intervention (15, 33). Based on the previous study (15), two frequency bands, μ (10–12 Hz) and β (18–24 Hz) bands, will be used for the calculation of PDC. The PDC values will be normalized to a range of 0–1 and then averaged across each participant. Ten consecutive MEPs will be recorded for each stimulus intensity to measure the changes in corticomotor function. These measurements will determine each subject’s average ICI and ICF responses by calculating the mean of 10 trials of paired-pulse TMS. Statistical analyses will be performed using SPSS 21.0 (IBM SPSS Statistics, NY, United States), with the significance level set at *p* < 0.05.

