Earlier studies have shown the importance of the close relationship between motor intention and feedback (11–13). However, there is a lack of studies demonstrating the superiority of BCI operated using MI-contingent feedback (real BCI) over BCI operated using MI-irrelevant feedback (sham BCI). Two studies have only proven the superiority of real BCI over sham BCI. Ramos-Murguialday et al.’s study using BCI-driven finger orthosis (14) revealed a noteworthy enhancement in motor function, evident in the upper limb Fugl–Meyer assessment (FMA) scores of the real-BCI group compared to the sham-BCI group. In a separate study using FES as a feedback modality, Biasiucci et al. (15) also showed significant disparities in FMA improvement and wrist extensor muscle strength between real and sham BCI, favoring real BCI. However, these two studies enrolled only patients with chronic stroke. Thus, the favorable effects of real BCI were not confirmed in the subacute phase of stroke. Frolov et al. exhibited enhancements within a real-BCI group in patients with subacute and chronic stroke. However, they did not directly compare real-BCI and sham-BCI (16). Moreover, they did not enroll patients with subacute and chronic phase stroke separately at the beginning of the study. However, they analyzed them by categorizing them into subacute and chronic groups after the termination of the study.

A recent study demonstrated that functional recovery predominantly occurs within the first 2–3 months after stroke (17). Patients who undergo early rehabilitation therapy after a stroke tend to exhibit better outcomes, with significant recovery occurring within the early phase after stroke, such as the subacute phase (18, 19). Similarly, patients with subacute stroke benefit from training with a BCI. Wu et al. (20) demonstrated that the BCI significantly enhanced upper limb motor function and reorganized brain functional networks. Therefore, it needs to be verified whether real BCI is superior to sham BCI in the subacute phase of stroke. In this study, we aim to compare the effects of real and sham BCI on motor function and brain activity among patients with subacute stroke with weak wrist extensor strength.

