### Trial design

2.1

This intervention will be performed as a double-blind, parallel-group (1:1 ratio), randomized controlled trial. In addition, it will be conducted in an independent and quiet environment, where maximum concentration can be achieved with the BCI. The therapist will always be beside the participant in preparing for any issues during the intervention. We will assess the measures to determine the extent of improvement provided by the intervention over time. The CONSORT flow diagram is shown in Figure 1.

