## Conclusion

4

We hypothesize that contingency between MI-related neural correlates and rich sensory feedback is essential in closed-loop BCI systems for functional improvement and neural plasticity. Therefore, we aim to investigate whether differences in function and neural plasticity arise from the close contingent connection between MI-induced brain activity and the consequent feedback. We will compare the effects of the BCI system operated by MI-contingent feedback (real-BCI) versus MI-independent feedback (sham-BCI) on distal upper limb function and brain activity in patients with subacute stroke.

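### Section 2.11 specifies no between-arm test, although the trial's stated aim is to compare real with sham BCI

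*Protocol article*

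**What the plan says.** The Introduction gives the aim: "we aim to compare the effects of real and sham BCI on motor function and brain activity". The Abstract says the same and the Conclusion repeats real versus sham. Section 2.1 describes a "double-blind, parallel-group (1:1 ratio), randomized controlled trial".

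Section 2.11 then names four tests for outcomes:

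- **Normal data, main test:** "A repeated-measures analysis of variance at the time level (T0, T2, T4, and T8) will be applied to examine whether" the primary, secondary and neurophysiological outcomes got better after treatment.
- **Normal data, follow-up:** "Paired t-tests will be used as post-hoc tests to examine significant changes in different combinations of time points for the scores".
- **Non-normal data, main test:** "The Friedman test will be performed for within-group comparisons between time points for non-normally distributed data".
- **Non-normal data, follow-up:** "The Wilcoxon signed-rank test will also be used for within-group comparisons at each point in time".

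The EEG connectivity measure is likewise described as a before-and-after contrast. Kolmogorov–Smirnov is also named, but only to check normality. Bonferroni is to be used for multiple comparisons, and the significance level is 0.05. Section 2.4.2 and Table 1 place SoO, SoA and IMI at T4 only.

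**The concern.** The aim is a contrast between arms, while the tests listed are contrasts between visits. No arm effect, arm-by-time interaction, baseline-adjusted arm comparison or two-sample test is named anywhere in the article.

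This matters more here than in a stable population. The Introduction says that functional recovery falls mainly in the first two to three months after stroke. Eligibility runs from one week to six months after onset, and both arms also receive conventional upper-limb therapy. Change over time is therefore expected in both arms even if contingent feedback adds nothing. A test for change will tend to be positive whether or not real BCI is better than sham, and so the randomisation goes unused.

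The Introduction itself criticises an earlier study for showing gains in its real-BCI group without comparing it directly with sham. The tests listed in section 2.11 have the same gap.

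**Working it through.** **Step 1: classify the tests.** Four outcome tests are named, and all four are contrasts between visits in the same patients. None is a contrast between arms. For SoO, SoA and IMI there is one visit, so no visit contrast exists and none of the four tests can be used.

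**Step 2: inputs for an illustration.** From the protocol: 20 per arm, 40 in total; significance level 0.05; four visits. The number of visit pairs is 4 × 3 / 2 = 6, so Bonferroni over all pairs gives 0.05 / 6 = 0.0083. The protocol gives no SD, expected change or sidedness, and does not state how many pairs are corrected for. I therefore assume two-sided tests, correction over six pairs, and a range of changes. There is no planned power figure to reproduce, because section 2.5 says no calculation was done.

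**Step 3: separate tests in each arm, no true difference between arms.** Let d be the mean change divided by the SD of the change, equal in both arms. The power of one arm's paired t-test, p, comes from the noncentral t with 19 degrees of freedom and noncentrality d × √20. The arms are independent, so P(exactly one arm significant) = 2p(1 − p), and P(real BCI only) is half of that.

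| d (assumed) | p at 0.05 | exactly one arm, 0.05 | p at 0.0083 | exactly one arm, 0.0083 |
|---|---|---|---|---|
| 0.20 | 0.136 | 0.235 | 0.035 | 0.067 |
| 0.30 | 0.247 | 0.372 | 0.079 | 0.145 |
| 0.47 | 0.514 | 0.500 | 0.234 | 0.359 |
| 0.65 | 0.787 | 0.335 | 0.501 | 0.500 |
| 0.80 | 0.924 | 0.141 | 0.729 | 0.395 |
| 1.00 | 0.989 | 0.023 | 0.921 | 0.145 |

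Example: at d = 0.30 and 0.05, 2 × 0.247 × 0.753 = 0.372, and real only is 0.186. The maximum of 0.50 occurs where p is near one half, which is d ≈ 0.47 at 0.05 and d ≈ 0.65 at 0.0083.

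**Step 4: arms pooled.** With n = 40 and d = 0.5, the noncentrality is 0.5 × √40 = 3.16 on 39 degrees of freedom. Power is 0.87 at 0.05 and 0.65 at 0.0083. Every such positive result would be recovery common to both arms.

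**Step 5: the ANOVA with and without an arm term.** In a simulation, both arms followed the same course of 0, 0.3, 0.6 and 0.7 SD (SD of the outcome) at the four visits, with an assumed within-patient correlation of 0.6, 40 patients and 4,000 runs. The time effect was significant in 99.7% of runs and the group-by-time effect in 5.0%. Only the second holds its nominal error rate for the question that the trial asks.

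The t-test and ANOVA figures illustrate the logic. They are not predictions for a six-grade MRC score.

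**The case against.** The strongest defence is that the ANOVA sentence does not exclude a group factor. Within-group is written only for Friedman and Wilcoxon, and naming the time level may merely identify the repeated factor in a parallel-group trial. That reading is possible, though the stated purpose (improvement) and the paired follow-up tests count against it. It does nothing for the non-parametric route, which has no between-arm reading. That route may well be used for the primary outcome, an ordinal grade from 0 to 5 with entry restricted to grade 2 or below.

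A second defence is that this is a condensed article and an unseen analysis plan may hold the missing term. It may, so how the trial will actually be analysed is uncertain. But the article does set out its tests, in detail that extends to post-hoc procedures, and those it fixes do not match its aim.

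A third is that this is a pilot. Section 2.5 uses that status only to justify 20 per arm; the stated aim remains comparative.

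Two stronger readings are tempting and go too far. A reader might infer that the trial cannot answer its question. The documents do not support this: the randomised data would allow the comparison, and what is lacking is a named analysis. A reader might also infer that superiority will be claimed because one arm is significant and the other is not. No section says so; the figures in Step 3 show what such an inference would risk. Nor is the 50% maximum typical: with large recovery in both arms, discordance becomes rare at 0.05.

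**Conclusion.** The point stands as a mismatch between aim and stated analysis, and it should be fixed before analysis. No between-arm test is specified on either route, and SoO, SoA and IMI have no applicable test. The finding itself rests on the text alone and needs no assumed effect size.

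The size of the risk does depend on assumptions. With equal true change in both arms, 20 per arm and changes of 0.2 to 1.0 SD, exactly one arm is significant in 2% to 50% of trials at 0.05 and in 7% to 50% at 0.0083. The protocol gives no figure that would place the trial within those ranges.

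**What to change.** In section 2.11 and in any separate analysis plan:

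1. Name a between-arm primary analysis of affected wrist-extensor MRC grade at one pre-stated visit, adjusted for baseline MRC and suited to an ordinal scale, with a 95% CI. T4, the end of the intervention, is one candidate; the protocol does not rank the visits, so the choice is the sponsor's. A proportional-odds model or a rank-based two-arm test would serve.
2. For the other repeatedly measured outcomes, use a model with arm, visit, arm-by-visit and the baseline value, and report the arm difference at each later visit.
3. For SoO, SoA and IMI, name a two-arm test at T4.
4. Label the within-arm tests descriptive, and state that superiority will not be inferred from one arm being significant and the other not.

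The cost is rewording, with no extra patients or data. The change does not make the trial confirmatory: with 20 per arm and no dropout, a two-sided two-sample t-test at 0.05 has 80% power only for a difference of about 0.91 SD, and 34% power at 0.5 SD. The interval should therefore carry the interpretation.

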#### Exclusion criteria

2.2.2

The exclusion criteria are as follows: (1) factors impeding recording of electroencephalogram (EEG) signals such as skin infections, scalp wounds, and the presence of metal implants under electrodes; (2) spasticity of wrist flexor, scoring ≥2 on the modified Ashworth scale; (3) cognitive impairments or severe aphasia hindering the ability of the participant to understand and follow the instructions during the research; (4) presence of a neurological or psychiatric disorder other than stroke; (5) musculoskeletal problem or severe pain of the affected upper limb impeding intervention; (6) hemispatial neglect; (7) patients with epilepsy.

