#### Secondary outcomes

2.4.2

We will use the upper extremity of the FMA to assess the motor function of the upper extremity. The FMA evaluates body function encompassing a wide range of assessments. It is highly recommended for evaluating upper extremity function and activity in both research and clinical practice (23). Scores on this assessment range from 0 to 66. We will use the Modified Ashworth scale (MAS) to evaluate muscle spasticity (24). It consists of six points, as follows: 0, no tonus increase; 1, the presence of a catch-and-release feeling at the end of the range of motion or a slight tonus increase in character with minimal resistance; 1 +, there is a slight increase in muscle tone observed through minimal resistance throughout less than half of the joint range of motion; 2, muscle tone is increased throughout the range of motion of the whole joint, but the joints can be moved easily; 3, there is significant tonus increase, which makes passive movement difficult; and 4, the affected parts are rigid in flexion and extension. In addition, we will evaluate the active range of motion in the wrist extension/flexion. The Stroke Impact Scale (SIS) serves as a self-report evaluation for measuring stroke outcomes and is utilized for assessing Health-Related Quality of Life. It assesses eight domains (strength, hand function, mobility, activities of daily living, emotion, memory, communication, and social participation) on a 5-point scale (25). The Korean Version of the Stroke Rehabilitation Motivation Scale (K-SRMS) measures the degree of motivation in patients with stroke during rehabilitation interventions (26). It includes 24 items, and the responses to each item are measured on a scale of 1–5. It is categorized into seven subscales: extrinsic motivation (EM)-introjected (motivation from external factors leading to internal pressures, such as guilt), EM-regulation (motivation from external pressures or rewards, such as praise from others), EM-identification (motivation from activity participation for personal growth), amotivation (AM; absence of motivation), intrinsic motivation (IM)-knowledge (motivation from knowledge gained from the activity), IM-stimulation (motivation from enjoyment or pleasure of an experience), and IM-accomplishment (motivation from personal satisfaction with the activity accomplishment). We will assess the sense of ownership (SoO) and agency (SoA) using questionnaires to understand the experience of BCI in patients. SoO describes the feeling of mindedness toward one’s body parts, feelings, or thoughts. In contrast, SoA refers to the experience of initiating and controlling an action. SoO and SoA are utilized to assess users’ sense of ownership and agency over a virtual limb, as well as to regulate the movements of an artificial hand (27). SoO will be assessed using an 8-statement questionnaire and SoA, using a 16-statement questionnaire; of the 16 questions, eight belong to the FES agency, and the remaining eight belong to the VR agency. It is reported on a 7-point Likert scale ranging from −3 (“totally disagree”) to 3 (“totally agree”), whereby 0 indicates neither agreement nor disagreement (“neutral”). The IMI is a multidimensional measurement device intended to assess participants’ subjective experiences related to a target activity in laboratory experiments (28). It assesses seven subscales: (1) participants’ interest/enjoyment; (2) perceived competence; (3) effort; (4) value/usefulness; (5) felt pressure and tension; (6) social relatedness; and (7) perceived choice while performing a given activity. It is composed of a 45-item questionnaire 7-point Likert scale (ranging from “completely disagree” = 1 to “completely agree” = 7). The SoO and SoA questionnaires and IMI will be assessed only at immediately after the end of the intervention (T4).

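### The entry limit on wrist-flexor MAS leaves little room for improvement, so the planned within-group test of whether MAS improved says little about efficacy if it is null (minor)

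*Protocol article*

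**What the plan says.** Section 2.2.2 excludes patients with "spasticity of wrist flexor, scoring ≥2 on the modified Ashworth scale". Section 2.4.2 places MAS among the secondary outcomes: "We will use the Modified Ashworth scale (MAS) to evaluate muscle spasticity". It names no muscle. On the scale, "It consists of six points, as follows: 0, no tonus increase", followed by 1, 1+, 2, 3 and 4.

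Table 1 schedules MAS at T0, T2, T4 and T8 and puts it in the Primary block. Section 2.4.1 gives the MRC scale as the only primary outcome.

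Section 2.11 plans a repeated-measures analysis of variance over the four time points, which "will be applied to examine whether primary, secondary, and neurophysiology outcomes improved after the intervention", with paired t-tests between time points. For data that are not normal, "The Friedman test will be performed for within-group comparisons between time points for non-normally distributed data", with Wilcoxon signed-rank tests, also within group. On multiplicity, "The Bonferroni correction will be used for multiple comparisons". MAS is given no separate aim or method.

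**The concern.** The entry rule and the stated aim of the test pull in opposite directions. Eligibility keeps patients at the bottom of the scale, and the analysis then asks whether they moved further down. Two misreadings are at stake. First, no fall in MAS could be reported as no effect of the intervention on tone, when many patients had nowhere to fall. Second, a rise over time in both arms could be attributed to the training when it might partly reflect selection on a low score. Because Table 1 can be read as making MAS a primary outcome, either misreading could carry more weight than a secondary outcome deserves.

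**Working it through.** **Inputs from the protocol.** Six ordered grades, scored here 0 to 5 (section 2.4.2). Qualifying grades 0, 1 and 1+, that is scores 0 to 2 (section 2.2.2). Twenty patients per arm (section 2.5). Four time points. Significance level 0.05, with no side stated; two-sided is assumed. The protocol gives no MAS distribution, reliability or effect size, so there is no planned figure to reproduce.

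**Room to move.** From a qualifying score *s*, the largest possible fall is *s* (0, 1 or 2 grades) and the largest possible rise is 5 − *s* (5, 4 or 3 grades).

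**Patients able to improve.** With a share *f* at grade 0, this is 20 × (1 − *f*). If every eligible patient falls exactly one grade, the mean fall is 1 − *f*. The shares are assumptions.

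| Share at grade 0 | Able to improve, of 20 | Mean fall if all of them drop one grade |
|---|---|---|
| 35% | 13 | 0.65 |
| 50% | 10 | 0.50 |
| 65% | 7 | 0.35 |

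Over 30% to 70% at grade 0, the number runs from 14 down to 6.

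**What a within-arm test needs.** When *k* patients change, all in one direction, the exact two-sided signed-rank p-value is 2/2^*k*.
- *k* = 6: 2/64 = 0.031, the fewest changes that can reach 0.05.
- *k* = 7: 2/128 = 0.0156.
- *k* = 8: 2/256 = 0.0078, the fewest that can reach 0.05/6 = 0.0083. The six pairs of four time points are an assumption about how Bonferroni is applied.

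With 65% at grade 0, seven falls out of seven still miss the corrected limit in the exact test. The paired t-test is less strict: seven one-grade falls and thirteen zeros give mean 0.35, SD √(0.35 × 0.65 × 20/19) = 0.489, t = 0.35/(0.489/√20) = 3.20 on 19 df, p = 0.005.

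The picture also changes with more patients above grade 0. If 10 can improve, each with an assumed 70% chance of falling and nobody rising, P(at least 6 falls) = 0.85 and P(at least 8) = 0.233 + 0.121 + 0.028 = 0.38.

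**Regression to the mean.** This was simulated with a latent-normal tone score, three assumed grade distributions (31% to 63% of those admitted at grade 0), and no true change.
- If the T0 score is the qualifying score, the mean later shift is 0 at reliability 1.0, +0.06 to +0.13 grade at 0.9, +0.11 to +0.23 at 0.8 and +0.19 to +0.42 at 0.6. For reliability 0.9 to 0.6, a paired t-test in one arm of 20 shows a false rise in about 5% to 29% of trials, against a nominal 2.5%.
- If MAS is measured afresh at T0 with independent error, the shift from T0 onward is 0.00. The rise has already happened between screening and T0, and 4% to 22% would score 2 or more at T0.

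Table 1 has eligibility screening under Enrolment and MAS under a separate Baseline column. The text does not say whether the screening score is reused.

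**The case against.** Four objections have force.

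- **Muscle.** The exclusion caps only the wrist flexor, and section 2.4.2 names no muscle. If other upper-limb muscles are scored, the cap does not apply to them. Wrist flexor is the natural reading in a wrist-extension trial, but it is an assumption.
- **Direction.** A reader might infer that the plan looks only for improvement and would miss worsening. The document does not support that: analysis of variance and the Friedman test have no direction, the post-hoc tests are not stated to be one-sided, and a rise in MAS would be tested too. What remains is that the stated question is improvement.
- **Certainty of a null.** A reader might infer that a finding of no improvement is all but guaranteed. The figures above contradict this unless the share at grade 0 is high, and even there it depends on using an exact test with Bonferroni.
- **Drift.** A reader might infer that MAS must rise after entry through selection alone. That needs T0 to be the qualifying score, or measurement fluctuations that persist to T0, and Table 1 separates screening from baseline. The sizes rest entirely on assumed inputs. Randomisation applies the same selection to both arms, so a comparison of real with sham would largely cancel any drift.

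It can also be said that the lack of a between-arm test in section 2.11 is a general matter. That is true, but the floor makes its effect on MAS specific. None of these objections removes the floor at qualification or the conflict over the Primary label.

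**Conclusion.** The point holds as a minor one about a single secondary outcome. Provided MAS is scored on the wrist flexor, grade-0 entrants cannot improve and no one entering at 0, 1 or 1+ can fall more than two grades. A null within-group result would then say little about efficacy. How little depends on the share at grade 0, which the protocol does not give: between 6 and 14 of 20 per arm could improve for assumed shares of 70% down to 30%.

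Upward drift within both arms is a conditional risk whose size cannot be derived from the document. The contradiction between Table 1 and sections 2.4.1 and 2.4.2 on whether MAS is primary needs no assumption.

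**What to change.** - **Sections 2.4.2 and 2.11:** code MAS as six ordered grades. Compare real with sham BCI at T4 and T8 by an ordinal or exact rank method that takes account of the baseline grade.
- **Reporting:** give changes in both directions, including the number in each arm whose grade rises.
- **Interpretation:** state that, because of the entry limit, absence of MAS improvement is not evidence about efficacy.
- **Definitions:** state which muscle is scored and whether the T0 score is a fresh reading or the screening score.
- **Table 1:** move MAS out of the Primary block.

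Turning MAS into a yes/no worsening endpoint is not required and would have low power at 20 per arm: about 21% for 15% against 35% with Fisher's exact test.

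The cost is wording only, with no new data or visits. The small downside is giving up a within-group efficacy claim on MAS.

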#### Inclusion criteria

2.2.1

The inclusion criteria are as follows: (1) hemiplegic participants secondary to a first-ever stroke with lesions confined to one hemisphere; (2) subacute stroke, which is defined as motor dysfunction occurring within 1 week to 6 months after stroke onset; (3) Medical Research Council (MRC) scale of affected wrist extensor muscle strength ≦ 2; (4) age > 19 years; and (5) a patient who has the cognitive ability to understand and follow the instructions of the researcher.

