#### Primary outcomes

2.4.1

The MRC scale will be used to test the wrist strength (22). The MRC score ranges from 0 to 5 as follows: grade 0, no visible contraction; grade 1, visible contraction without movement of the limb; grade 2, movement of the limb but not against gravity; grade 3, the movement against gravity over (almost) the full range; grade 4, the movement against gravity and resistance; and grade 5, normal.

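### The analysis of the ordinal MRC grade hangs on a Kolmogorov–Smirnov normality test that cannot tell the reader anything useful about a six-grade scale

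*Protocol article*

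**What the plan says.** Section 2.4.1 names one primary outcome, the MRC grade of wrist strength: "The MRC score ranges from 0 to 5 as follows: grade 0, no visible contraction", and so on up to grade 5 (normal). Each step is a qualitative description. Section 2.2.1 admits only patients with "Medical Research Council (MRC) scale of affected wrist extensor muscle strength ≦ 2", so three values are possible at T0.

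Section 2.11 sets the default analysis: "A repeated-measures analysis of variance at the time level (T0, T2, T4, and T8) will be applied to examine whether primary, secondary, and neurophysiology outcomes" show gains over time. It adds: "Paired t-tests will be used as post-hoc tests to examine significant changes in different combinations of time points for the scores". Normality is then checked: "The normality of the data will be checked using Kolmogorov–Smirnov tests, and the results will show whether the data are normally distributed". The alternative route follows: "The Friedman test will be performed for within-group comparisons between time points for non-normally distributed data", with the signed-rank test alongside. MRC is not exempted from this sequence. Neither is MAS, whose six ordered levels are 0, 1, 1+, 2, 3 and 4 (section 2.4.2).

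**The concern.** The article fixes a rule under which a normality test decides how an ordinal primary outcome is analysed. The rule is unsound for two reasons.

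- **The question has a known answer.** A variable with three possible values at T0 and six afterwards is not normally distributed. Rejection reports what the scale already implies. Non-rejection reports only that 20 observations did not reveal it, so the statement that the test results will show normality is wrong for this outcome.
- **The default route needs equal spacing.** ANOVA and t-tests on grades treat the step from no contraction to visible contraction as equal to the step from movement against gravity to movement against resistance. A normality test does not address that assumption.

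At stake is whether the primary analysis is one that suits the scale and is known before the data arrive. Repeated-measures ANOVA and the Friedman test each use all four visits together. If the pre-test accepts some visits and rejects others, the stated rule does not lead to one analysis.

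**Working it through.** The plan gives no figure to reproduce: section 2.5 reports that no sample size calculation was possible. The check asks how often a Kolmogorov–Smirnov (K-S) test lets MRC grades pass as normal.

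**Inputs from the article.** Grades 0–5 (2.4.1); at most 2 at entry (2.2.1); 20 per arm (2.5); significance level 0.05 (2.11).

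**Assumptions.** The article gives no grade distributions, so these are illustrative. T0: grades 0, 1, 2 equally likely. T4: grades 0–5 at 20/20/20/20/15/5%. Two common forms of the test are used: uncorrected, with the mean and SD estimated from the sample and the asymptotic p-value; and with the Lilliefors correction for that estimation.

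**Step 1: distance from normality.** D is the largest gap between the grade distribution and a normal curve with the same mean and SD.
- T0: mean 1, SD √(2/3) = 0.816. The largest gap is at grade 0: 1/3 − Φ(−1/0.816) = 0.333 − 0.110 = 0.223.
- T4: mean 0.20 + 0.40 + 0.60 + 0.60 + 0.25 = 2.05. Variance 6.45 − 2.05² = 2.2475, so SD 1.499. The largest gap is at grade 1: 0.40 − Φ(−1.05/1.499) = 0.400 − 0.242 = 0.158.

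The 5% critical value at n = 20 is 1.358/√20 = 0.304 uncorrected. It is about 0.192 with Lilliefors (95th percentile of D in 20,000 simulated normal samples). The T0 gap of 0.223 lies between the two, so the two forms tend to disagree on the same data. The T4 gap of 0.158 lies below both, and sampling variation carries many samples over the lower limit.

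**Step 2: simulated non-rejection at 0.05** (at least 2,000 samples per setting; repeat runs agree within about 2 to 3 percentage points)

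| Setting | Uncorrected | Lilliefors |
|---|---|---|
| T0, n = 20 | about 0.80 | 0.00 |
| T4, n = 20 | 0.99 | about 0.45 |
| T4, n = 40 (arms pooled) | 0.85–0.88 | 0.02–0.03 |

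Other assumed shapes at n = 20, from rejection rates (non-rejection = 1 − rejection):
- T0 at 60/25/15%: 1 − 0.87 = 0.13 uncorrected, 0.00 Lilliefors.
- Grades 0–5 at 10/20/30/25/10/5%: 1 − 0.02 = 0.98 and 1 − 0.63 = 0.37.
- Grades 0–5 uniform: 1.00 and 1 − 0.49 = 0.51.

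**Step 3: four correlated visits in one arm.** A latent normal score was cut into six grades, with rising means and T0 capped at 2 (n = 20, 2,000 runs). The uncorrected test flagged no visit in 71% of runs and all four in 0%, so visits disagreed in 100 − 71 = 29%. Lilliefors flagged at least one visit in every run and all four in 39%, so visits disagreed in 100 − 39 = 61%.

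**Step 4: does the gate inflate type I error?** Under a true null, 20 per arm, 4,000 runs, both forms of K-S, on the T4 distribution above and on a skewed one (40/25/15/10/7/3%):
- between-arm t-test or Mann–Whitney chosen by K-S: 0.047–0.055;
- paired t-test or signed-rank chosen by K-S: 0.040–0.047;
- the same tests without a gate: 0.038–0.055.

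No inflation is visible. The four-visit ANOVA was not tested.

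**The case against.** The strongest reply has four parts.

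- **Error rates.** A reader might infer that choosing the test by a pre-test breaks the nominal 5%. The article contains nothing that shows this, and step 4 found gated and ungated tests alike. That stronger reading is not supported.
- **Pre-specification.** A reader might infer that the method is left open. It is not: section 2.11 names two routes and the condition between them. The unit of testing and the version of K-S are details that an article may leave to a fuller document, and their absence is not the fault raised here. The fault is the stated condition, which remains unsound however those details are filled in. The contrast between K-S versions shows only how little the result says about the data.
- **Between-arm comparison.** A reader might infer that the gate is what confines the analysis to within-group tests. It does not: the ANOVA is also described only over time, with paired post-hoc tests, so neither route names a test of real against sham BCI. That is a separate issue, and removing the gate alone would leave it in place.
- **Weight.** This is a pilot with a sample size taken from a pilot-trial minimum, and t-tests and rank tests had similar error rates in the simulations. That limits the consequence and justifies a moderate rating. It does not rescue the gate.

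**Conclusion.** The point holds in a limited form. Section 2.11 sends an ordinal primary outcome through a normality test that cannot inform the choice of method, and it reads non-rejection as evidence of normality. At n = 20 the chance that MRC grades pass runs from 0% to about 80% in the equal-thirds T0 case and from about 45% to 99% in the T4 case, according to the version of the test. The route can also differ between visits of one arm.

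These percentages rest on assumed grade distributions and are illustrative. The conclusion that a scale with three to six values is not normal needs no simulation. MAS shares the fault: its level 1+ has no natural numeric score. If it is scored on the wrist flexor, the exclusion of scores of 2 or more (2.2.2) also leaves three levels at T0.

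The change should be made. It does not stop a pilot from running, and the case for it does not rest on a loss of type I error control.

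**What to change.** For MRC and MAS, delete the normality gate in section 2.11 and name in advance one ordinal or rank-based comparison of real with sham BCI at T4 that uses the baseline grade. Any one of these would do:

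- proportional-odds regression of the T4 grade on arm and baseline grade, reporting the common odds ratio with a 95% confidence interval, with adjacent sparse grades merged by a rule stated beforehand;
- a van Elteren test stratified by baseline grade;
- a rank-ANCOVA with the baseline grade as covariate.

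Also remove the statement that the Kolmogorov–Smirnov results will show whether the data are normal. Changing the models for the Fugl-Meyer score and active range of motion is optional and not needed for this point.

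Cost: wording only, with no new data, visits or participants. The effect measure will be less familiar to clinicians than a mean change. With 20 per arm, some grades may be sparse and the proportional-odds assumption can hardly be checked, which is a reason to consider the rank-based options.
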